## Methods

### Overview

The design, conduct, and reporting of the study will adhere to the Standard Protocol Items: Recommendations for Interventional Trials (SPIRIT) [69], Consolidated Standards of Reporting Trials (CONSORT) guidelines [70], and Consolidated Standards of Reporting Trials of Electronic and Mobile Health Applications and Online Telehealth (CONSORT-EHEALTH) [71].

### Study Location

Malaysia is the context of this study since it is the host country for many international students coming from different countries. The target participants in this study will be those new international postgraduate students joining Malaysian public universities. The study includes 20 well-known public universities that attract large numbers of new international students who will be screened according to the inclusion criteria.

### Study Design

This study is quantitative in nature and experimental in design. Specifically, the study employs a cluster randomized controlled trial (RCT) design. Figure 1 summarizes the study design. Selection of such an experimental design is based on its strength and effectiveness [72]. A cluster design will be employed as the randomization and intervention at the level of the university, and the primary outcome measures are related to students’ acculturative stress, while the secondary outcomes refer to their adjustment and intention to drop out of university. Public universities will be randomized to either a control (wait-list) or intervention (educational intervention) group. In order to determine the effectiveness of the intervention program, the primary and secondary trial outcomes will be assessed through surveys of new international postgraduates at 3 time points: baseline (time 1) before the intervention, immediately postintervention (time 2), and at 3-month follow-up after the intervention (time 3).

**Figure 1 figure1:**
[figure not shown]
Flowchart of study.

### Participants

Public universities that will be eligible to participate in the study should satisfy the following criteria: acting or serving as the main campuses for international students in Malaysia and having more than 40 new international postgraduates in their first semester in Malaysia. For students, only new international postgraduates entering the selected universities in their first academic semester will be eligible to participate.

### Recruitment

For the purpose of eligibility assessment, the researcher will approach all public universities in Malaysia and invite only those universities that are eligible through formal invitation letters issued by the researcher’s university. The letters will be directed to the high authorities of the selected universities through emails seeking their permission for the researcher to conduct his study among international postgraduates. Moreover, the researcher will obtain lists of new international postgraduates joining these universities, including necessary information about the students including contact details, faculty, nationality, and academic program.

Procedures for recruiting public universities will be based on several strategies that have been reported to be useful for maximizing research participation, including prenotifying universities of the study, providing opportunities for participation, visiting persons in charge at the universities, contacting potential participants using telephone and other contact methods, accessing research staff for further clarification on participation, and using dedicated research staff to manage the recruitment process. Specifically, an invitation letter will be directed to a university contact person (deputy vice chancellor for academic and international affairs, deputy vice chancellor for research and innovation, and dean of postgraduate studies) in each eligible university.

Once the letters are sent, the above-mentioned persons in the universities will be contacted by telephone to confirm eligibility based on inclusion criteria and assess interest in participating in the study. This will be followed by several calls until the decision on informing international postgraduates of participation in the study is made and the researcher is informed of such decision. However, such decision, in some cases, will be made through meeting among academic and research staff and consultation with the management committee of a given university. At the end of this process, a confirmation email will be sent to each university, confirming and thanking them for agreement to participate in the study. Each participating university will be given hard and electronic copies of the information and invitation letters for the selected postgraduates in that university.

Student recruitment will use a random sampling procedure to select students from the list of the new postgraduates for each selected university based on probability proportional to size method in order to reduce possible sampling bias. The respondent’s information and consent sheets will be given to the sampled students to get their agreement to participate. In order to maximize response rates, representatives of the international students will be requested to seek the selected postgraduates’ consent.

### Randomization and Blinding

Prior to randomization, the researcher will start collecting baseline data. This will be followed by assigning the universities as the unit of randomization. Universities will be randomized in order to reduce contamination between groups [73,74]. However, to ensure allocation concealment, the allocation sequence of the universities selected at the previous stage will be assigned to a control group and an intervention group by the ratio 1 to 1. The purpose of this is to ensure that the number of universities allocated to each group will remain approximately equal (see Figure 1 flowchart) [75-77]. This will be achieved by employing a simple randomization procedure. The researcher will use a computer-generated list of random numbers. It is exclusive to the researcher who will allocate the 10 universities to the two groups. In addition, no one in the control groups will know what the experimental groups will be offered. The statistician who will perform the primary analyses will be blinded to group allocation. This study will follow a CONSORT chart [73] as shown in Figure 1 (study flowchart).

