**Methods:**

A cluster randomized controlled trial design with Malaysian public universities as the unit of randomization will be used in this study. Public universities will be randomized in a 1:1 ratio to be either in the intervention (educational program) or control group (waiting list). Participants in the intervention group will receive 7 sessions in 9 hours delivered by an expert in psychology and the researcher. The control group will receive the intervention once the 3-month follow-up evaluation is completed.

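### Simple randomization of 10 universities cannot secure the near-equal arms it is meant to give, and a 1:1 ratio with a list held by the researcher is not allocation concealment

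*Protocol article*

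**What the plan says.** All but two of these statements are in the protocol article, Randomization and Blinding.

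- Timing: "Prior to randomization, the researcher will start collecting baseline data". Assignment of the universities follows.
- Ratio: to secure allocation concealment, the universities "will be assigned to a control group and an intervention group by the ratio 1 to 1".
- Purpose of the ratio: to "ensure that the number of universities allocated to each group will remain approximately equal".
- Method: "This will be achieved by employing a simple randomization procedure". No blocking, stratification, matching or fixed total is stated.
- Custody of the list: "The researcher will use a computer-generated list of random numbers", and "It is exclusive to the researcher who will allocate the 10 universities to the two groups".
- Delivery (Abstract, Methods): "Participants in the intervention group will receive 7 sessions in 9 hours delivered by an expert in psychology and the researcher". The Recruitment section has the same researcher approach the universities and obtain the student lists.
- Number of clusters: 10 in Randomization and Blinding, but Study Location says "The study includes 20 well-known public universities that attract large numbers of new international students".

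The statistician for the primary analyses is to be blinded to allocation.

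**The concern.** The stated purpose and the stated method do not fit together. Simple randomization assigns each unit independently and fixes no totals. With many units the arms come out nearly equal in proportion; with 10 they often do not. Unequal arms cost power in a trial that has few clusters to begin with.

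The concealment claim fails for a different reason. Concealment depends on who can know or influence the next assignment, and a ratio has no bearing on that. Here one person approaches the clusters, collects baseline data, holds the list, makes the allocation and co-delivers the sessions. Because baseline collection need only have started before allocation, the text does not exclude students being consented and surveyed once their university's arm is known. The outcomes are self-reported, so if enrolment differed by arm the comparison would be biased directly.

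**Working it through.** **Reproducing the plan's sample size.** Inputs from Sample Size: means 2.58 and 2.07 (difference 0.51), SD 1.08, cluster size 40, ICC 0.05, attrition 20%. The article does not state the power; two-sided 5% and 80% reproduce its figure.

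- n per arm = 2 × (1.960 + 0.842)² × 1.08² / 0.51² = 70.4, rounded up to 71.
- Design effect = 1 + 39 × 0.05 = 2.95; 71 × 2.95 = 209.45, given as 209 per arm.
- 209 / 0.8 = 261.25, given as 261 per arm and 522 in total.

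**Distribution of the split.** Under simple randomization the number of universities in one arm is Binomial(10, 0.5), with 2¹⁰ = 1024 equally likely outcomes.

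| Split | Calculation | Probability |
|---|---|---|
| 5:5 | 252/1024 | 24.6% |
| 6:4 | 2 × 210/1024 | 41.0% |
| 7:3 or worse | 2 × (120 + 45 + 10 + 1)/1024 | 34.4% |
| 8:2 or worse | 2 × (45 + 10 + 1)/1024 | 10.9% |

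So 6:4 or closer occurs in 24.6% + 41.0% = 65.6% of draws. With the 20 universities of Study Location, an exact 10:10 split has probability 17.6%, and 13:7 or worse has 26.3%.

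**Power by split.** Take 209/5 = 41.8 analysed students per university, giving a design effect of 1 + 40.8 × 0.05 = 3.04. For a:b universities, SE = 1.08 × √[(3.04/41.8)(1/a + 1/b)]. Power is from the noncentral t on 10 − 2 = 8 degrees of freedom (two-sided 5%), with noncentrality 0.51/SE.

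| Split | SE | Variance relative to 5:5 | Power |
|---|---|---|---|
| 5:5 | 0.184 | 1.00 | 68.0% |
| 6:4 | 0.188 | 1.04 | 66.3% |
| 7:3 | 0.201 | 1.19 | 60.6% |
| 8:2 | 0.230 | 1.56 | 49.5% |

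Power at 9:1 is 31.0%, and 10:0 counts as zero. The weighted average over all splits is 0.246 × 68.0 + 0.410 × 66.3 + 0.234 × 60.6 + 0.088 × 49.5 + 0.020 × 31.0 = 63%. The average loss against a fixed 5:5 draw is therefore about 5 points. With 40 per university, power at 5:5 is 67.4% and the average is 62.5%, so the loss is again about 5 points.

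**Chance baseline imbalance.** Assume the ICC of 0.05 also applies at baseline. With 5:5 and 209 per arm, the SD of the between-arm difference in a baseline mean is √(2 × 3.04/209) = 0.171 SD units, a 95% range of ±0.33. The target effect is 0.51/1.08 = 0.47. This is computed with the arms already equal. For a university-level covariate, the chance of a difference above 0.5 cluster-SD is 42.9% at 5:5 against 45.5% averaged over simple randomization, so fixing the split changes it very little.

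**The case against.** **Rough equality is all that is promised.** This is correct. If 6:4 counts, simple randomization meets the aim in 65.6% of draws. A computer-generated list might also be a random permutation cut at five, which would give 5:5. But the text calls the procedure simple and states no such restriction, and a method that misses its aim in 34.4% of draws does not secure it.

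**The power cost is modest.** This also stands. The commonest unequal split costs about 2 points and the average loss is about 5. The 50% figure needs an 8:2 split. A reader might put the whole shortfall from 80% down to the randomization method; the 68% at 5:5 comes from having 10 clusters and 8 degrees of freedom.

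**Baseline imbalance.** A reader might infer that simple randomization is what exposes the trial to baseline differences approaching the target effect. The figures do not support this: the ±0.33 range is for equal arms and comes from few clusters with no stratification. The Statistical Analysis section also includes time 1 in the GEE and adjusts for covariates, which deals with part of it.

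**Safeguards exist.** Universities are selected before allocation, students are sampled at random from lists, representatives seek their consent, dedicated staff manage recruitment, questionnaires are self-administered and the analyst is blinded. These limit selection of universities and analysis bias. They do not put the sequence in independent hands or settle when baseline ends. A reader might infer that the plan intends enrolment after allocation; it does not say so. The wording on starting baseline collection is ambiguous and leaves that possible.

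**Conclusion.** The point holds in two parts. First, the stated randomization method does not deliver the stated purpose: with 10 universities the split is 7:3 or worse in about one draw in three, and the average power loss is about 5 points (68% to 63%). Second, the 1:1 ratio does not conceal allocation, and no independent custody of the list is described to take its place.

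The probabilities are exact for 10 universities. The power figures rest on the plan's difference, SD and ICC, 41.8 analysed students per university and a cluster-level t test on 8 degrees of freedom. The counts of 10 and 20 universities contradict each other and must be reconciled; the mismatch between method and purpose remains under either.

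The document does not establish that recruitment bias will occur, or that fixing the split would remove chance baseline imbalance. Even so, the correction should be made before allocation, because allocation cannot be repaired afterwards.

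**What to change.** Replace simple randomization with one fixed-total draw: 5 of 10 universities, or half of the final number once the two counts are reconciled. Make it on coded university identifiers, after consent and baseline are complete in every university, and state that order explicitly. Preferably have it made by someone with no part in recruitment, data collection or delivery. Drop the statement that the ratio provides concealment and describe instead who holds the list and when it is released. The cost is a short script, a one-off task for a colleague outside the study team, and waiting for the last university to finish baseline.

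As an optional further improvement, stratify or constrain the draw on university size or mean baseline ASSIS and adjust for the same variables in the model. This addresses the chance imbalance that an equal split leaves. It is one option among several and is not needed to resolve the contradiction. Balancing on ASSIS also means waiting for scored baseline data from all universities, which takes time in a population recruited in its first semester.

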### Sample Size

The total sample size needed will be calculated by applying the formula for two population means [78] as seen in Figure 2. Means and standard deviation used for the intervention group and control group were based on the estimation offered in a previous RCT [79]: µ1=2.58, µ2=2.07, SD1=1.08, SD2=1.08, n1=24, n2=30. Therefore, the total sample (n) will account for 71 participants. Calculation of the required sample size in this study was performed based on the guidelines in the CONSORT for cluster RCTs [73]. By considering the account intraclass correlation coefficient (ICC), it is necessary to multiply the sample size in RCTs by design effect=1+(m–1)*ICC, where m is the average cluster size [80-83]. Thus, the average class size is assumed to be 40 participating students, and an ICC of .05 could be expected. This would result in design effect N=1+(m–1)*ICC=1+(40–1)*.05=2.95. Based on the sample size required by the formula, the required minimum sample size for each group after adjusting for design effect is n=71*2.95=209, and the total sample size required is 209 participants per arm.

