**Figure 2 figure2:**
[figure not shown]
Sample size formula for two population means.

To factor in 20% attrition, if (n) is the sample size required as per formula and (d) is the dropout rate, adjusted sample size N new is obtained as N1=n/(1–d) [84]. Therefore, the total required per group after adjusted for dropout rate is N1=209/(1–0.2)=261; hence, a total of 522 new international postgraduate students will be needed for the sample size in both groups.

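### The number of universities is given as both 20 and 10, the sample size is tied to neither, and with 10 the power is 79% by the normal approximation but about 68% on 8 degrees of freedom

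*Protocol article*

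**What the plan says.** All places are in the Methods of the protocol article.

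- **Study Location:** "The study includes 20 well-known public universities that attract large numbers of new international students".
- **Randomization and Blinding**, on the computer-generated list: "It is exclusive to the researcher who will allocate the 10 universities to the two groups". Allocation is 1:1 by simple randomisation of universities.
- **Sample Size, inputs:** "µ1=2.58, µ2=2.07, SD1=1.08, SD2=1.08, n1=24, n2=30", taken from an earlier randomised trial, followed by "Therefore, the total sample (n) will account for 71 participants".
- **Sample Size, clustering:** "the average class size is assumed to be 40 participating students, and an ICC of .05 could be expected". This gives a design effect of 2.95, and then "the required minimum sample size for each group after adjusting for design effect is n=71*2.95=209".
- **Sample Size, attrition:** 209 is divided by 0.8 to give 261 per group, so that "a total of 522 new international postgraduate students will be needed for the sample size in both groups".
- **Participants:** a university is eligible if it has more than 40 new international postgraduates in their first semester.
- **Statistical Analysis:** a GEE over three time points, adjusted for covariates, taking account of clustering within universities.

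The Sample Size section gives no number of universities, and the text states no power.

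**The concern.** The university is the unit of randomisation, and in a cluster trial the number of such units largely determines power. Two different counts are printed, and the sample size rests on a cluster size that has meaning only once the count is fixed. A reader cannot tell which trial is being run, or what power it has.

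The calculation also takes a per-group number built on normal quantiles and multiplies it by a design effect. With 10 universities, a between-group comparison has only 8 degrees of freedom at the level of randomisation. A normal reference is optimistic there, and an uncorrected GEE with five clusters per arm tends to inflate the type I error. If the true power is well below what the calculation implies, a null result could be misread as evidence that the programme does not work.

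Finally, 71 is called a total but is used per group. Someone checking the chain could conclude that the trial is twice as large as needed, when it is not.

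**Working it through.** **1. Reproduce the article's chain.** Difference 2.58 - 2.07 = 0.51 and SD 1.08, so d = 0.51/1.08 = 0.472.

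n per group = 2(1.96 + 0.8416)² × 1.08²/0.51² = 70.4, which rounds up to 71.

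Other settings give 56 (one-sided 5%, 80% power), 95 (two-sided, 90%) and 77 (one-sided, 90%). So 71 is a per-group number at two-sided 5% and 80% power.

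Design effect: 1 + 39 × 0.05 = 2.95. Then 71 × 2.95 = 209.45 (given as 209), 209/0.8 = 261.25 (given as 261), and 2 × 261 = 522. Analysed in total: 2 × 209 = 418. The rounding down is immaterial.

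**2. Match the chain to a number of universities.**

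| Reading | Arithmetic | Consequence |
|---|---|---|
| 10 universities, 40 = analysed | 418/40 = 10.45 | Roughly fits; 522/10 = 52.2 to enrol at each, while eligibility guarantees only more than 40 |
| 10 universities, 40 = enrolled | 10 × 40 = 400 | 122 short of 522 |
| 20 universities, 418 analysed | 418/20 = 20.9 | Design effect 1 + 19.9 × 0.05 = 1.995, not 2.95 |

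**3. Power.** With k universities per arm and m analysed in each:

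- design effect DE = 1 + (m - 1) × 0.05
- effective n per arm = km/DE
- noncentrality = 0.472 × √(effective n/2)

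The result is referred to the normal distribution (critical value 1.96) or to a noncentral t on 2k - 2 degrees of freedom (critical value 2.306 on 8).

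For k = 5 and m = 41.8: DE = 3.04, effective n = 209/3.04 = 68.75, noncentrality = 2.77.

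| Universities | Analysed per university | DE | Power, normal | Power, t (df) |
|---|---|---|---|---|
| 10 | 41.8 (418 in total) | 3.04 | 79.1% | 68.0% (8) |
| 10 | 32 (40 enrolled, 20% lost) | 2.55 | 75.3% | 64.1% (8) |
| 20 | 20.9 (418 in total) | 1.995 | 92.8% | 89.8% (18) |

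**4. Effect of baseline adjustment.** The documents give no correlation between baseline and outcome. As an assumption, let it be r, with the variance multiplied by 1 - r² at both levels. For 10 universities with 41.8 analysed, power on 8 degrees of freedom is 68% at r = 0, 72% at r = 0.3, 80% at r = 0.5 and 86% at r = 0.6. Spending one further degree of freedom on the covariate (7 left) gives 78% at r = 0.5.

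**The case against.** The best defence is that 10 is the design and that the calculation fits it. The design effect is applied before the attrition inflation, so 40 is most naturally the analysed cluster size. That gives 10.45 universities and, by the article's own approximation, 79% power, within two points of the inferred 80%. This stands, and it rules out saying that neither count fits. A reader might divide 522 by 40 and infer a third count of 13, but that needs 40 to mean enrolled students, which is the weaker reading.

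The 20 may be the set of universities considered and the 10 those selected. Recruitment does describe approaching all public universities and inviting the eligible ones, and Figure 1 is not shown. But Study Location says the 20 are included, and the screening it mentions is of students. The wording needs reconciling whichever was meant.

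The eligibility floor of 40 does not contradict an average intake of 52. It only fails to guarantee it.

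The 68% is for a comparison without covariates, whereas the article plans an adjusted GEE on repeated measures. This also stands: with a strong enough baseline correlation, 80% is reachable on 8 degrees of freedom. But the sample size claims no such gain. A small-sample correction may be specified in a fuller plan that is not shown, so its absence from the article is not held against it here.

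A reader might also infer a further loss from unequal cluster sizes, because students are sampled "based on probability proportional to size method in order to reduce possible sampling bias". That wording does not settle how many students each university contributes, and the documents give no variation in cluster size, so no figure can be attached.

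**Conclusion.** The point holds in a limited form. The printed counts of 20 and 10 are unreconciled, the sample size is linked to neither, and 71 is mislabelled as a total. These follow from the text alone, apart from the inferred 80% power behind 71.

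On power, the supportable statement for 10 universities and 418 analysed is 79% by the normal approximation and about 68% on 8 degrees of freedom. It falls to about 64% if 40 are enrolled and 32 analysed per university. These figures assume d = 0.472, ICC 0.05, two-sided 5%, a 5:5 split, equal cluster sizes and no gain from covariates.

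A reader might infer that the conflicting counts cause the drop to 68%, or that the trial is shown to be underpowered. Neither is supported. The drop comes almost entirely from having few clusters, and the gain from baseline adjustment is unknown. What is established is that the calculation as written does not support 80% power for a small-sample-valid, unadjusted test on 10 universities. Reconciling the count is essential, because the same 522 students would give about 90% if 20 universities were randomised.

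**What to change.** 1. State one number of universities to be randomised and use it in Study Location, Randomization and Blinding, and Sample Size. If 20 is the number considered, say so.
2. Say whether 40 means enrolled or analysed students, and recompute the design effect with the analysed cluster size that matches the chosen count (3.04 at 10 universities, 1.995 at 20, with 418 analysed). If 10 are kept, state that about 52 must be enrolled at each on average and whether the selected universities can supply them.
3. Label 71 as per group, and state the significance level and power behind it in the text.
4. Restate the power with a t reference on (universities - 2) degrees of freedom: about 68% at 10, or about 90% if 20 are in fact randomised with the same 522 students. If a gain from baseline adjustment is claimed, give the assumed correlation and its source.

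The cost is rewording and a less favourable stated power at 10 universities. No extra enrolment is required. Randomising more universities is optional, and would add delivery sites.
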